| 14.2. Audit report .....                                                            | 53 |
| 14.3. Final report and publication .....                                            | 53 |
| 15. Ethical, legal and administrative aspects .....                                 | 53 |
| 15.1. Legal requirements for the study .....                                        | 53 |
| 15.2. Patient information and informed consent .....                                | 54 |
| 15.3. Patient insurance .....                                                       | 54 |
| 15.4. Data protection and medical confidentiality.....                              | 54 |
| 15.5. Filing of data .....                                                          | 54 |
| 15.6. Legal aspects .....                                                           | 54 |
| 15.7. Good Clinical Practice (GCP) .....                                            | 55 |
| 15.8. Funding of the study .....                                                    | 55 |
| 15.9. Compliance with the protocol and protocol amendments .....                    | 55 |
| 16. References .....                                                                | 56 |
| 17. Annexe .....                                                                    | 58 |

Scientific background for the study: ALS is a neurodegenerative disease of adult onset caused by selective degeneration of motor neurons in the cortex and the spinal cord. The degeneration of motor neurons results into progressive paralysis of the limbs, speech, swallowing and respiratory muscles. ALS is always fatal and patients die of respiratory insufficiency between 3 and 5 years after diagnosis. So far, Riluzol (Sanofi-Synthelabo-Aventis) is the only approved medication that results into a minor prolongation of life (1.5 to 2.5 months). Riluzol is an inhibitor of the presynaptical release of glutamate. Another effect of Riluzol is the inhibition of glutamate release in activated microglia.

Neuroinflammation is an essential pathogenicity factor of motor neuron degeneration. Inflammatory changes can be found in sporadic ALS, the autosomal dominant form of ALS as well as in the SOD1-mouse model of the ALS. This can be demonstrated morphologically through the accumulation of activated microglia, astrocytes, and T-cells. At the biochemical level, these changes are accompanied by the activation and release of the proinflammatory cytokine Interleukin (IL)-1. The inflammatory mediator IL-1 mediates the recruitment and activation of phagocytic cells and induces an immune response. The bioactivity of IL-1 is physiologically controlled by the naturally occurring, highly selective Interleukin-1-Receptor-Antagonist (IL-1RN).

On the basis of the neuroinflammatory changes in ALS there is a scientific rationale for a clinical trial with ANA, which has anti-inflammatory pharmacological effects. ANA is a recombinant IL-1RN (r-metHuIL-1RN) which directly and selectively inhibits IL-1.

The primary study target implies the safety and tolerance of ANA in combination with Riluzol in ALS patients. An open tolerability study aims at testing whether a subcutaneous injection of 100 mg ANA is tolerated. This tolerability study will be the basis of a phase IIb/III efficacy study.

Tested medication: Trial medication: ANA (Kineret®) 100 mg of injectable solution in a ready-to-use pre-filled syringe in combination with an oral dose of 100 mg Riluzol. Open treatment with 100 mg ANA + 100 mg Riluzol.

Comparative medication: none

Study design: One arm study to assess the safety and tolerance of 100 mg ANA for the duration of 52 weeks in combination with Riluzol.

Schedule: Recruitment of patients: 11-2010 until 04-2011; duration of study: 52 weeks. Termination of clinical trial: 04-2012

Total number of patients: Treatment of 20 patients with 100 mg ANA in combination with 100 mg Riluzol. The biometric determination of cases numbers results into 17 analyzable patients, allowing a statistically proven effect of the primary endpoint. A screening of 30 – 60 patients is required to recruit 20 patients for the study.

Total number of centers: 1

Study population: patients with Amyotrophic Lateral Sclerosis (ALS)

Inclusion criteria

- patients aged  $\geq 18$  years and  $\leq 80$  years.

- clinical diagnosis of ALS (revised El Escorial criteria) with dominant affection of the 2nd motor neurons or the clinical ALS variant of a progressive muscle atrophy (PMA).
- clinical signs of a dysfunction of the 2nd motorneuron in at least one anatomic region outside the bulbar region.
- sporadic and familiar ALS.
- onset of symptoms with pareses from six months up to four years before inclusion in the study.
- treatment with Riluzol 100 mg/day at least for 3 months before termination of study.
- written informed consent (according to AMG §40 (1) 3b).
- ability to communicate, either in person or by an authorized person.
- ability to communicate, either verbally, manually or through an electronic communication system.
- internet access, either personally or by an authorized person.
- refrigerator facilities for ready-to-use pre-filled ANA-syringes at home.

Page 7 in the German text

- no participation in any other clinical trial during this study schedule.
- negative pregnancy test or at least 24 months postmenopausal.

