#### Statistical evaluation:

The primary objective of this pilot study is tolerability and the secondary endpoints should allow, concurrently, to establish conditions to plan a statistically justifiable phase II efficacy study, is a proof of tolerability and several secondary endpoints.

Primary and several secondary endpoints will first be examined exploratively and evaluated descriptively. The conceptual study will be carried out with n=20 patients.

Similar scientific questions have been described in the literature with a comparable number of patients. Secondary endpoints will be examined by parametric or non-parametric tests depending on scaling and distribution type. The biometric evaluation will be done by SAS®.

Page 33 in the German text

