### **6.1. Main target criterion**

*Primary objective of the study:*

Examination of number and severity of adverse events (UE), severe adverse events (SUE), adverse drug reactions (ADR), unexpected adverse drug reactions (uADR), severe adverse drug reactions (SADR), Suspected Unexpected Serious Adverse Reaction (SUSAR), and pathological laboratory parameters.

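### The synopsis promises statistical proof on the primary endpoint from 17 patients, while its own statistical section describes an exploratory and descriptive evaluation

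*Protocol*

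**What the plan says.** All of the following is in the Protocol.

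- **Synopsis, total number of patients.** The plan is "Treatment of 20 patients with 100 mg ANA in combination with 100 mg Riluzol". The size is then justified by a calculation: "The biometric determination of cases numbers results into 17 analyzable patients, allowing a statistically proven effect of the primary endpoint".
- **Synopsis, study design and comparative medication.** "One arm study to assess the safety and tolerance of 100 mg ANA for the duration of 52 weeks in combination with Riluzol", with "Comparative medication: none".
- **Synopsis, targets, and section 6.1.** The primary endpoint covers seven categories. Section 6.1 opens the list with "Examination of number and severity of adverse events (UE), severe adverse events (SUE), adverse drug reactions (ADR" and goes on through unexpected and serious reactions and SUSARs to pathological laboratory values. No category is given a rate, limit or success rule.
- **Synopsis, statistical evaluation.** "Primary and several secondary endpoints will first be examined exploratively and evaluated descriptively". Tests appear only for the other endpoints: "Secondary endpoints will be examined by parametric or non-parametric tests depending on scaling and distribution type". The size of 20 is supported with "Similar scientific questions have been described in the literature with a comparable number of patients". A grammatically broken sentence in the same section also speaks of proving tolerability, without a criterion.
- **Section 6.3, study organization.** Drop-out of at most 10% is expected and is said to be built into the number of patients already.
- **Table of contents.** Sections 13.1 (case numbers) and 13.2.1 (hypotheses) are listed, but the text available ends at section 8.7.2.

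**The concern.** One synopsis gives two accounts of the same thing. In the first, a calculation fixes 17 analysable patients so that something about the primary endpoint can be proven. In the second, the primary endpoint is explored and described, and the number of patients rests on what others have used. A descriptive summary of safety counts does not have the property that the first account claims for it.

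The synopsis makes this study the basis for a later phase IIb/III efficacy trial. If the sentence stands, a report with few or no serious reactions could cite the protocol as saying that tolerability was statistically established, when the data would bound event rates only loosely.

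**Working it through.** **1. The two accounts side by side**

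| | Total number of patients | Statistical evaluation |
|---|---|---|
| Basis of the size | biometric calculation, 17 analysable | precedent in the literature, 20 patients |
| Primary endpoint | effect statistically proven | explored and described |
| Tests | implied for the primary endpoint | named for secondary endpoints only |

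The rows do not agree. The statements in the synopsis and in section 6 that the size is unsuitable for efficacy do not resolve this, because the primary endpoint is safety.

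**2. Can the 17 be reproduced?** No. That would need a tested rate, a limit or alternative, alpha and power, or else a precision target. The available text gives none of these. Only the drop-out step can be checked:

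- 17 / (1 − 0.10) = 18.9, so 19 patients.
- 20 × (1 − 0.10) = 18 analysable patients.
- 1 − 17/20 = 15% loss.

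The figures 17 and 20 differ from the 10% assumption by one patient either way. That is compatible with generous rounding and is not a finding.

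**3. Could 17 patients in one arm support a test at all?** Yes, if a rate and a limit are fixed. A search over exact binomial rules, on a 5-point grid of assumed rates, finds 17 as the smallest size for these null and alternative pairs:

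- 0.30 against 0.60 (one-sided alpha 0.05, power 0.80; rule: at least 9 of 17);
- 0.30 against 0.65, and 0.60 against 0.90 (0.05, 0.90);
- 0.50 against 0.85, and 0.55 against 0.90 (0.025, 0.90).

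None of these rates is in the document. A test is therefore possible in principle, but several unrelated hypotheses give the same 17, so the number does not reveal what would be tested.

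**4. What the sizes deliver descriptively.** The inputs are n = 20 treated and n = 17 analysable, both from the synopsis. The incidences p = 5% and 10% are assumptions for illustration.

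- One-sided 95% upper bound with no event: 1 − 0.05^(1/n).
- Two-sided exact 95% upper limit with no event: 1 − 0.025^(1/n).
- Chance of seeing at least one event: 1 − (1 − p)^n.

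| | n = 20 | n = 17 |
|---|---|---|
| Upper bound, 0 events, one-sided 95% | 13.9% | 16.2% |
| Upper limit, 0 events, two-sided 95% | 16.8% | 19.5% |
| Seen at least once, p = 5% | 64% | 58% |
| Seen at least once, p = 10% | 88% | 83% |
| Never seen, p = 5% | 36% | 42% |
| Never seen, p = 10% | 12% | 17% |

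With three affected patients, the exact 95% interval is 3.2% to 37.9% for 3/20 and 3.8% to 43.4% for 3/17.

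**The case against.** The strongest defence is that the missing inputs may exist. Sections 13.1 and 13.2.1 are in the contents, and both the synopsis and section 6.3 refer to a calculation. A reader might infer that the plan has no hypothesis and no tolerability limit. The documents do not support that, because those sections are not available. This part of the defence stands in full.

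A reader might also infer that a one-arm study without a comparator can never prove anything about its primary endpoint. That is wrong as well: a rate can be tested against a fixed limit in one arm, and 17 patients suffice under some assumed rates.

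Two smaller points also stand. The statistical paragraph says the endpoints are *first* explored, which does not exclude a later step. The fragment about proving tolerability comes from a garbled, translated sentence and carries little weight.

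Finally, the study is called a pilot and section 6.3 promises only first information on tolerability, which makes over-reading less likely. The precision figures show what a descriptive reading can deliver; they do not measure the contradiction.

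None of this removes the conflict. If section 13 holds a confirmatory hypothesis, the statistical paragraph of the synopsis is incomplete or wrong. If it does not, the claim attached to the 17 patients is wrong.

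**Conclusion.** The point holds as an internal contradiction in the synopsis, of moderate weight. The property claimed for the sample size is not one that the stated primary evaluation has, and the available text gives no tested rate, limit, alpha or power that would supply it. Nothing is claimed about the content of section 13, and the one-arm design is not itself the fault.

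If the evaluation is descriptive, the study excludes only fairly high incidences: above 13.9% with 20 patients or 16.2% with 17 when no event is seen. An assumed 5% reaction would go unseen in more than a third of such studies.

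These figures assume independent patients and a per-patient incidence over the period actually observed. The protocol's endpoint is worded as number and severity, so they describe one natural summary of it and not the whole endpoint. Enrolment and conduct are unaffected; what changes is what the report may conclude.

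**What to change.** Reconcile the passages, depending on what section 13 says.

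**If the primary evaluation is descriptive**, as the synopsis's statistical section states, remove the claim of a statistically proven effect, clarify the sentence that speaks of proving tolerability, and insert a precision statement such as:

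> No hypothesis on the primary endpoint is tested. With 20 treated (17 analysable) patients, a reaction that is not observed has a one-sided 95% upper bound on its incidence of 13.9% (16.2%). A reaction with an assumed true incidence of 5% is seen at least once with probability 64% (58%), and one with 10% with probability 88% (83%).

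**If section 13 holds a confirmatory hypothesis**, state in the synopsis which category is tested, its rate, the limit, alpha and power, show how they give 17, and correct the statistical evaluation paragraph to match.

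The cost is a wording change and no extra patients. The downside of the first option is that the stated capability of the study becomes less favourable.

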#### Exclusion criteria:

- diagnosis of ALS with dominant affection of the 1st motor neurons without clinical signs for a concomitant dysfunction of the 2nd motor neurons in at least one anatomic region outside the bulbar region (clinical variant of a spastic ALS).
- diagnosis of a clinical ALS-variant of a primary lateral sclerosis (PLS).
- patienten with known hypersensitivity to ANA, Riluzol or one of the adjuvants.
- clinical severe hypoventilation syndrome with a vital capacity < 50 %.
- pregnant or breast-feeding women.
- women of childbearing age who are not using or cannot use any highly effective contraceptives (Pearl-index <1).
- clinical significant modifications of the ECG including symptomatic bradycardia.
- continuous non-invasive ventilation with a ventilation free period < 2 hours.
- Tracheotomy and mechanical ventilation.
- Laboratory parameters outside the standard range and equivalent to a clinical significant cardiovascular, pulmonological, hematological, hepatological, metabolic and kidney disease.
- malignant tumors.
- severe renal impairment (creatinine-clearance < 30 ml/min).
- previous history of recurrent infection or an underlying disease that predisposes to infections.
- severe neutropenia (absolute number of neutrophils < 1,5 x 10^9/l).
- monoclonal gammopathy of uncertain significance.
- infectious diseases including tuberculosis, HIV, hepatitis B and C.
- patients with severe clinical co-morbidities including psychiatric diseases.
- dementia and lack of capacity for consent.
- clinical diagnosis of epilepsy or an epileptic seizure.
- treatment with any other study medication < 3 months prior to study inclusion.
- diseases or malfunctions which exclude participation at the study at the treating investigator's discretion.
- non-cooperation.
- all contraindications concerning the study medication (inclusive adjuvants of the dosage form).
- non-cooperation regarding storage and disclosure of pseudonomized data in the context of the clinical trial.

- combined use of ANA and Etanercept or other TNF-antagonists.
- internment at a judicial institution (according to AMG §40 (1) 4).

Targets: The primary target of the study is the examination of safety and tolerability of a subcutaneous injection of ANA together with an oral dosis of Riluzol in ALS patients. The choice of sample size is not appropriate for securing the effectiveness of ANA in combination with Riluzol in ALS. However, by means of secondary endpoints the influence of the ANA treatment on the ALS progression rate and life quality will be studied.

*Primary endpoints:*

Examination of number and severity of

- adverse events (AE).
- severe adverse events (SAE).
- adverse drug reactions (ADR).
- unexpected adverse drug reactions (uADR).
- serious adverse drug reactions (sADR).
- suspected cases of unexpected serious adverse drug reactions (SUSAR).
- pathological laboratory parameters.

*Secondary endpoints:*

- evaluation of long term tolerance and pharmaceutical drug safety of ANA in combination with Riluzol.
- number of patients in need of a continued, non-invasive ventilation or tracheostoma supported invasive ventilation.
- number of patients in need of a percutaneous endoscopic gastrostomy (PEG.)
- number of patients who have completed a treatment with ANA in combination with Riluzol.
- evaluation of the clinical efficacy of ANA on the progression rate of pareses and functional limitations in ALS by comparison to the evaluation of the intra-individual progression rate of the revised *ALS Functional Rating Scale* (ALS-FRS-R) over a study period of 52 weeks and the progression rate prior to the participation in the study ( $\Delta$  ALS-FRSR).
- evaluation of the efficacy of ANA on the respiratory function in ALS, which is determined by a forced vital capacity in the course of 52 weeks.

- evaluation of the efficacy of ANA on the respiratory function in ALS patients, who are subject to a non invasive mask ventilation (determination of ventilation time per day).
- determination of survival time or timing of a tracheotomy because of respiratory insufficiency (apart from elective tracheotomy or to control secretions).

Safety

Information, consent, and documentation:

- the patient will be given written information on the application of the medication, its risks, the importance of a contraception, and appropriate methods for safe contraception.
- written consent of the patient to participate in the study.
- written confirmation from the patient that the information on the study has been read and understood.
- documentation of information and written consent.

Women in childbearing age who did not have a hysterectomy, and whose menopause was less than 24 months before the initiation of the study will have to have a pregnancy test prior to treatment with the study. Women in childbearing age also have to use a highly effective

contraception method (defined as Pearl Index < 1) (pill, contraceptive coil, hormone implant, transdermal patch, a combination of two barrier methods (condom and diaphragm)), a sterilization or sexual abstinence at least one month prior to the first application of the study medication and for the whole duration of the treatment.

Measures to be taken prior to the treatment of women in childbearing age

- pregnancy test in the urine
- discontinuation of therapy in case of proof of pregnancy

Page 12 in the German text

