#### Termination of the study:

A premature termination of the study is possible under the following conditions:

- a patient suffers of a severe infection which is possibly, likely, or certainly caused by the study medication and cannot be explained in the context of the underlying clinical condition.
- new and reproducibly scientific findings on ANA during the course of the clinical study show the inferiority of the treatment with ANA
- evidence of increasing number of serious adverse events

The PI of the clinical trial will decide on the termination of the study.

After termination the following events will be documented and communicated to the sponsor of the study:

- all serious adverse events which have incurred within 30 days after the last treatment with ANA

- Any pregnancy which has been confirmed within 84 days (12 weeks) after the last dosis of ANA .

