## **8.2. Treatment regimen**

### **8.2.1. Instructions for application:**

#### **Dosage, timing and duration of administration of ANA:**

The trial consists of a continuous treatment with 100 mg Riluzol and a dose of 100 mg ANA/day for the duration of 52 weeks. The medication is consumed daily (1 pre-filled Kineret 100 mg syringe). The patients receive a combination treatment with 100 mg Riluzol. The treatment with Riluzol is carried out as basic medication and pre-treatment during the whole period of treatment, the dose remains unchanged.

ANA is supplied by the Swedish company Orphan Biovitrum AB. The pharmacy at the study center supplies the drug to the patient's address and is in charge of maintaining the cold chain. At home the drug is kept in the refrigerator (2°C - 8°C). The patient will receive an individual injection training in the study center before start of the treatment.

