#### **Measures required for contraception:**

Female patients who indicated that they did not have a hysterectomy or whose menopause is not longer than 24 months ago, have to get medical advice by a physician regarding risk assessment of a pregnancy and – where appropriate - regarding contraceptives. These patients have to use reliable contraceptives at least one month before start of treatment with ANA, during the whole treatment period, and one month after termination of treatment. Reliable contraceptives are the simultaneous use of a highly effective method of contraception such as intrauterine pessary, hormonal contraceptives, tubal ligation, vasectomy in the partner) and at least one additional effective method (diaphragm, pessary, cervical cap, or latex condom in the male partner).

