#### **Prescription procedure for ANA:**

The safety requirements of the announcement of the Drug Commission of the German Medical Association imply the following measures:

- detailed information to the patient.
- therapy risks.
- ANA must not be distributed to other persons.

Page 38 in the German text

- The patient must not donate blood during and at least one month after termination of ANA treatment

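### The synopsis accepts a single contraceptive option with a duty stated only through treatment, while section 8.2.1 requires two simultaneous methods until one month afterwards

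*Protocol*

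**What the plan says.** **Synopsis, Safety.** Women of childbearing age must use one highly effective method, defined by a Pearl Index below 1. The examples are pill, coil, implant, patch and "a combination of two barrier methods (condom and diaphragm". Sterilization and abstinence are accepted as well. The last option and the period are worded "sexual abstinence at least one month prior to the first application of the study medication and for the whole duration of the treatment". Nothing is said about the time after the last dose.

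**Section 8.2.1, Measures required for contraception.** The period is "at least one month before start of treatment with ANA, during the whole treatment period, and one month after termination of treatment". The standard is "Reliable contraceptives are the simultaneous use of a highly effective method of contraception", with an intrauterine device, hormonal methods, tubal ligation and partner vasectomy as examples, "and at least one additional effective method (diaphragm, pessary, cervical cap, or latex condom in the male partner". Diaphragm and condom appear only in the second group. Abstinence is not mentioned.

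**Related text.**
- The exclusion criteria (synopsis and section 7.2) bar women who do not or cannot use highly effective contraception with a Pearl Index below 1. They name no second method and no duration.
- Section 8.2.1 also restricts blood donation: "The patient must not donate blood during and at least one month after termination of ANA treatment".
- The synopsis (Termination of the study) asks for reporting of "Any pregnancy which has been confirmed within 84 days (12 weeks) after the last dosis of ANA".
- Section 9.9 (Pregnancy) is listed in the table of contents, but its text is not available to this review.

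**The concern.** Both texts are current and both read as obligations. The synopsis does not merely shorten 8.2.1. It gives its own list of sufficient options and its own period, and one of those options (condom plus diaphragm) is built entirely from methods that 8.2.1 treats as supplementary.

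What is at stake is participant protection. Both the synopsis and 8.2.1 make contraception part of the written patient information. If that text, or the center's staff, work from the synopsis, women will be asked for less than 8.2.1 demands. Compliance also becomes a matter of which page is read, and the synopsis lists significant protocol violation and lack of compliance among the possible grounds for discontinuing a patient.

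**Working it through.** The protocol gives no figure to reproduce and no error rate or sample size is involved, so the check is a side-by-side reading.

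**Step 1: who is covered.** The two places describe the women slightly differently. A woman of childbearing age without hysterectomy who has not passed the menopause falls under both, so the rules do meet in the same person.

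**Step 2: the two rules.**

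| Element | Synopsis, Safety | Section 8.2.1 |
|---|---|---|
| Methods at one time | one option from the list | one highly effective plus one further effective method |
| Condom plus diaphragm alone | sufficient | not sufficient; both are second methods only |
| Abstinence | accepted | not addressed |
| Start | at least one month before first dose | at least one month before first dose |
| End | stated through treatment only | one month after treatment |

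**Step 3: each synopsis option against 8.2.1.** The synopsis offers seven options.
- Pill, coil, implant, patch and sterilization (5) have no second method.
- Condom plus diaphragm (1) has no highly effective method.
- Abstinence (1) is not addressed in 8.2.1.

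5 + 1 + 1 = 7, so no synopsis option, used alone as written, clearly satisfies 8.2.1.

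**Step 4: the period.** Treatment is a "dose of 100 mg ANA/day for the duration of 52 weeks".
- Synopsis: 1 month + 52 weeks + 0.
- Section 8.2.1: 1 month + 52 weeks + 1 month.
- Difference: one month, all of it after the last dose.

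**Step 5: can both be obeyed?** On duration, yes: a woman who continues for the extra month also meets the synopsis. On methods, a woman using a hormonal method plus a condom meets both. The reverse fails. A woman on the pill alone who stops at her last dose meets the synopsis and breaches 8.2.1 on both counts. The conflict thus lies in what the synopsis accepts as enough.

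**Step 6: does other text decide between them?** The exclusion criteria set an entry threshold compatible with either rule. The blood-donation rule supports a post-treatment month only by analogy. Neither it nor the pregnancy-reporting rule bears on one method versus two.

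**The case against.** The strongest reply is that a synopsis is a summary and 8.2.1 is the operative section. It stands under the instructions for application and requires the women concerned to receive a physician's advice on pregnancy risk and, where appropriate, on contraceptives. There are further safeguards: the entry exclusion, a pregnancy test before treatment, and discontinuation if pregnancy is shown. On duration the synopsis is silent rather than permissive, since it nowhere says that contraception may stop at the last dose. The document is also a translated extract, so its exact lists of methods should not bear much weight. And the Pearl Index standard appears in the synopsis and in both sets of exclusion criteria, while only 8.2.1 asks for two methods, so the sponsor's intention on number is not proven.

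Much of this stands. The duration difference is an omission in the shorter text rather than a flat contradiction, the option count in the working is illustrative, and the choice of two methods is the sponsor's to confirm. It does not remove the point. A summary may leave detail out, but naming condom plus diaphragm as sufficient is a different rule, and one method against two simultaneous methods does not turn on a translator's choice of word.

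A reader might also infer that the 84-day reporting window shows how long contraception ought to last, and that the synopsis leaves that whole window uncovered. The documents do not support this. The window concerns pregnancies confirmed in that time, which includes conceptions during treatment that are detected later. It is a reporting period and need not match a contraception period; the one month in 8.2.1 does not match it either.

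**Conclusion.** The point holds as an inconsistency in a stated participant-safety rule. Following the synopsis alone, a woman can breach 8.2.1 on the number of methods and miss the post-treatment month. The size is one option against two simultaneous methods, plus one month after the last dose.

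The practical reach is small and partly unknown: one center, at most 20 treated patients, and no stated number of women of childbearing potential. No endpoint, sample size or analysis changes. Actual harm is not shown. It depends on whether the patient information or the site follows the synopsis, and the documents at hand do not tell. The conclusion also assumes that the unseen section 9.9 does not set a precedence. Even if it did, the weaker wording would still stand in the synopsis.

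**What to change.** Put the 8.2.1 rule into the synopsis and the patient information: a highly effective method and a further effective method at the same time, from at least one month before the first ANA dose until one month after the last. Remove condom plus diaphragm as sufficient alone. Add one sentence, in both places, on whether abstinence may replace the two methods.

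If the sponsor instead intends a single method with a Pearl Index below 1, it should say so in both the synopsis and 8.2.1, and keep the one-month post-treatment period in both.

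The exclusion criteria and the 84-day pregnancy-reporting window can stay as they are. The cost is wording in the protocol and the patient information, with no added visits or patients and no change to the analysis.
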